### Data analysis

All analyses will be conducted using the intention to treat principle. We will describe baseline characteristics by study groups and test for differences in age, gender, PTSD symptoms, depressive symptoms, suicide risk, chronic pain, medical co-morbidities, co-morbid mental health disorders and other patient attributes. If noted, we will account for significant differences in the analyses.

Analysis of objective one, primary outcome: We will test the primary hypothesis by comparing dichotomous variables, self-reported quit attempts as the outcome variable at the end of the intervention period (3 months) and the end of the follow-up period (6 months post-intervention) between the two study arms using chi-square tests. Then, to account for potential imbalance in baseline characteristics and to improve the precision of estimates, we will test the primary hypothesis using a logistic regression model with quit attempts as the outcome variable and include baseline characteristics, tobacco dependence, selected baseline variables, and study group as independent variables.

Analysis of objective one, secondary outcomes: Changes in readiness stages and smoking cessation will be compared between arms using chi-square tests. Then, to improve the precision of estimates, we will test the secondary outcomes using a logistic regression model. This model will use the changes in stage of change and smoking cessation as the dependent variables and baseline characteristics, tobacco dependence, selected baseline variables, and study group as independent variables.

Analysis of objectives two and three, primary outcomes: We will test the primary objectives for objectives two and three by comparing means (or changes in means) of continuous variables, patient’s perception of care coordination and PTSD symptoms at the end of the intervention period (3 months) and the end of the follow-up period (6 months post-intervention) between the two study arms using the Student’s t-test. Then, to account for any imbalance in baseline characteristics and to improve the precision of estimates, we will test the primary objectives of these hypotheses using a multiple linear regression model. This model will use the perception of care coordination primary outcome as the dependent variable (and PTSD symptoms) and include baseline characteristics, tobacco dependence, selected baseline variables, and study group as independent variables.

Analysis of outcomes for objectives two and three, secondary outcomes: Mean scores (or changes in the mean scores) of standardized instruments will be used to assess depression, suicide risk, chronic pain, and health related quality of life in all subjects. These are all continuous outcomes so we will use the t-tests and linear regression to determine intervention effects.

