### Outcome measures

The study has three objectives; each has a primary outcome and secondary endpoints. Secondary outcomes are exploratory and supportive of the primary outcomes.

In objective one, we will compare the (1) proportion of individuals that make a self-reported 24-hour quit attempt, (2) progression through the stages of change [25,26] and (3) 7-day point prevalence quit smoking rates for the intervention group to usual care alone. The primary outcome is the proportion of participants making a self-reported quit attempt in each group during the study period. Secondary outcomes are the proportions of individuals who make a progression in their stage of change and quit smoking, as measured by a 7-day point prevalence, between study entry, end of intervention (month 3) and at 6 months post-intervention (month 9). Quit attempts will be bioverified by expired carbon monoxide levels (a CO level of less than or equal to ten will be considered non-smoking) [27] during in-person visits at the 3 month and 6 month follow-up periods. Subjects who do not respond will be classified as continuing smokers.

In objective two, we will compare the patient perception of care coordination for the intervention group to usual care alone. The primary outcome is the mean score change of the participant’s perception of care coordination (PACIC) [28,29] from baseline to end of intervention (month 3), and 6 months post-intervention (month 9) periods. Secondary endpoints of interest are an evaluation of the intervention from the participants’ perspective via two satisfaction surveys (one for stage-based/MI smoking cessation Health Buddy written content and one for the nurse-driven MI intervention). Patient satisfaction will be evaluated for the intervention group only at the end of the intervention (month 3).

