In objective three, we will compare PTSD symptoms of participants who receive the intervention to those receiving usual care alone. The primary outcome is the mean score change of PTSD symptoms utilizing the Posttraumatic Stress Disorder Checklist [30] from baseline to end of intervention (month 3), and 6 months post-intervention (month 9). Secondary endpoints of interest are the mean score change for the following survey results and will be compared from baseline to end of intervention (month 3) and 6 months post-intervention (month 9):Depression: Change in depressive symptoms measured by the Geriatric Depression Screen (GDS) [31,32]Chronic Pain: Change in chronic pain symptoms measured by the McGill Short Form Pain Questionnaire [33]Health Status: Change in the Health Care Related Quality of Life measured by the Veterans Rand-12 (VR-12) [34,35]

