Sample size calculations were based on testing the effectiveness of the intervention, compared to the control group, in higher rate of quit attempts and progression in the stage of change, better perceived care coordination, and improved PTSD symptoms. Only the trend of quit rate differences will be examined since the study sample will include those who are not ready to quit. Initially we expected to enroll 140 subjects in order to obtain 120 completers, anticipating a 12-15% drop out rate. However, due to a higher than expected loss to follow up rate enrollment was expanded to target 180 participants. Statistical analyses will be done using SAS (Cary, NC). Objective one involves comparison of two proportions for self-reported quit attempt rate and stage change rate. With 120 subjects, equally allocated between the two groups, 24% absolute difference in rates at 3 months can be detected for a two-sided test of proportions between two groups at a 5% Type I error rate and 80% power. Objective two and three involve comparison of means across two groups for perceived care coordination and PTSD symptoms. Effect size of 0.1, 0.25 and 0.4 (or equivalently mean difference of 0.2, 0.5, 0.8 in standard deviation units between two groups) are typically defined as small, medium, and large. By recruiting the 120 subjects for objective one, a medium effect size in perception of care coordination and PTSD symptoms can be detected for a two-sided test of means between two groups at a 5% Type I error rate and 80% power. We will consider this finding to be clinically significant if intervention group Veterans perceive their care to be better coordinated and they experienced less PTSD symptoms.

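### The care-coordination and PTSD symptom scores are defined as change from baseline, but the test is left open between means and changes, no deciding test is named, and the baseline score is not a named covariate

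*Protocol article*

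**What the plan says.** In the protocol article, Outcome measures defines both endpoints as changes. For objective three, "The primary outcome is the mean score change of PTSD symptoms" on the PTSD Checklist. For objective two, the PACIC score is likewise assessed as a change "from baseline to end of intervention (month 3), and 6 months post-intervention (month 9) periods".

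Data analysis opens with "All analyses will be conducted using the intention to treat principle". For objectives two and three it then plans two steps:

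- Student's t-tests at the end of the intervention and at the end of follow-up, "comparing means (or changes in means) of continuous variables".
- Multiple linear regression: "to account for any imbalance in baseline characteristics and to improve the precision of estimates, we will test the primary objectives of these hypotheses". The model will "include baseline characteristics, tobacco dependence, selected baseline variables, and study group as independent variables".

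Neither step is named as the deciding one. The baseline PACIC or PTSD Checklist score is not listed as a covariate, although Data collection shows that both are measured at baseline.

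The only rule for non-response concerns smoking: "Subjects who do not respond will be classified as continuing smokers". On retention, the sample size text at the end of Outcome measures says that "due to a higher than expected loss to follow up rate enrollment was expanded to target 180 participants".

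**The concern.** Three features combine.

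1. **Open outcome form.** The endpoint is a change, but the test may use final means or changes. These are different tests and can disagree on the same data. With two candidate forms and a following regression, and no statement of which one decides, the result to be reported can be chosen after the data are seen.
2. **Baseline score not named.** The baseline value of the same scale is usually the strongest predictor of the follow-up value. A t-test on final means ignores it. A t-test on changes subtracts it with a fixed coefficient of one, which costs precision unless the correlation is very high.
3. **Loss to follow-up.** A t-test or ordinary regression at one visit, as named, can use only participants with a score at that visit. Each visit is analysed alone, so a month-3 score tells the analysis nothing about a missing month-9 score. The smoking rule cannot be applied to a continuous score.

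At stake are the power and error rate of two of the three objectives, and whether their estimates describe everyone randomised.

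**Working it through.** **Inputs from the article:** 120 subjects allocated equally (60 per arm), two-sided 5% level, 80% power, medium effect of 0.5 SD; enrolment of 140 for 120 completers, later raised to 180. **Assumed:** correlation r between baseline and follow-up score (the article gives none), with equal variances at the two times.

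**Step 1. The plan's own figure.** For two means at 60 per arm and 0.5 SD, the normal approximation gives 78.2% power and the exact t-test 77.5%. The smallest difference detectable with 80% power is 0.51 SD by the normal approximation and 0.52 SD by the exact t-test. The plan's claim therefore holds as a rounding.

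**Step 2. Precision of the three forms.** Variance of the treatment estimate relative to a t-test on final means:

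- final means: 1
- changes: 2(1 − r)
- adjusted for the baseline score: 1 − r²

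The ratio of adjusted to change is (1 + r)/2, which is below 1 for every r below 1. Exact t power at 0.5 SD divided by the square root of the factor, 60 per arm:

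| r | Change factor | Adjusted factor | Power, final means | Power, changes | Power, adjusted |
|---|---|---|---|---|---|
| 0.4 | 1.20 | 0.84 | 77.5% | 69.8% | 84.2% |
| 0.5 | 1.00 | 0.75 | 77.5% | 77.5% | 88.0% |
| 0.6 | 0.80 | 0.64 | 77.5% | 85.9% | 92.4% |

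Which t-test form is better depends on r. Baseline adjustment is better than both in every row.

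**Step 3. Cost of leaving the form open.** Simulation with 60 per arm and 40,000 trials per setting:

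- With no effect, counting a trial as significant if either t-test form gives p < 0.05 yields a type I error of 9.0%, 9.2% and 9.3% at r = 0.3, 0.5 and 0.7, for one time point.
- With a true 0.5 SD effect, the two forms disagree on significance in about 26%, 24% and 23% of trials at r = 0.4, 0.5 and 0.6.

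**Step 4. Loss.** The initial plan implies 1 − 120/140 = 14.3%. If 120 completers were still the goal at 180, the implied loss is 1 − 120/180 = 33.3%. The article states no actual rate.

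**Step 5. Possible size of bias.** With equal loss in both arms, the effect among those observed differs from the effect in all randomised by (loss) × (difference in effect between observed and lost). For an assumed difference of 0.25 to 0.5 SD:

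- at 14.3% loss: 0.143 × 0.25 = 0.04 to 0.143 × 0.5 = 0.07 SD
- at 33.3% loss: 0.333 × 0.25 = 0.08 to 0.333 × 0.5 = 0.17 SD

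The design effect is 0.5 SD. These figures illustrate scale only, because nothing in the article fixes the assumed difference.

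**The case against.** The strongest reply has four parts.

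- **The regression already uses baseline.** The same paragraph plans a covariate regression expressly for precision. Baseline PTSD symptoms are among the characteristics to be compared between arms and may be meant to enter it, and the change form of the t-test also uses baseline. A reader might infer that the plan discards the baseline measurement; the text does not support that. What stands is narrower: the baseline score is not named, other covariates are open, and the regression is not said to decide.
- **No restriction to responders is written.** A reader might infer that the analysis is confined to responders and so is not intention-to-treat. The restriction follows only from the methods named. Comparing observed scores by randomised arm is not in itself a breach of intention to treat; it needs a missingness assumption. The article is condensed, so missing-data handling may sit in an unseen document, and its absence here is not a fault. What stands is that separate single-visit tests make poor use of the scores collected.
- **One-third loss is not reported.** A reader might take it as fact. It holds only if 120 completers remained the goal of the 180 target.
- **A mixed model is no cure.** It is biased too if loss depends on unobserved scores, and a participant lost before month 3 adds only a baseline value. Both are true. At month 3 the gain comes mainly from baseline adjustment; the benefit of joint modelling falls chiefly at month 9.

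**Conclusion.** The point holds as a matter of analysis choice and wording. The endpoint definition and the named test do not match, two candidate tests stand without a deciding one, and the baseline score is not named in the regression.

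Baseline adjustment raises power from 77.5% (final means) or 70 to 86% (changes) to 84 to 92%, at 0.5 SD and 60 per arm with assumed r of 0.4 to 0.6. The 9% type I error applies only if the form is chosen after seeing results; the article does not say that it will be. The direction of the precision gain does not depend on the exact r, but its size does.

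On missing scores, the documents support only that loss exceeded expectation and that the named tests use the scores observed at each visit. They establish neither a loss rate nor an actual bias.

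**What to change.** For PACIC and for the PTSD Checklist:

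1. Name one baseline-adjusted analysis as the deciding test. Preferred is a likelihood-based repeated-measures model of months 3 and 9 with arm by time, the baseline score adjusted for or constrained equal between arms, and all randomised participants with any score included.
2. Keep change from baseline as the endpoint and remove the open choice of form. With adjustment for the baseline score, final scores and changes give the same treatment estimate, so nothing is lost. Striking out only the reference to changes would be the wrong edit, because that is the part that matches the endpoint definition.
3. Keep the unadjusted t-test as supportive only.
4. State the missing-at-random assumption and add one sensitivity analysis to it, for example with missing intervention-arm scores following the control-arm pattern.

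The cost is a little more analysis work in SAS, which the plan already names, and an assumption that must be stated openly. No further participants, visits or measurements are needed.

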## Discussion

This study incorporates a written and verbal MI-based intervention by a nurse into a currently used home telehealth care coordination platform for Veterans with PTSD who smoke. We feel this program is unique and important for several reasons. One, it has the potential to facilitate utilization through increased access to smoking cessation care via use of telehealth and phone calls. This expands reach to Veterans who live at a significant distance from tertiary care centers or have difficulty obtaining clinic services due to PTSD symptoms or stigma. Two, it can potentially increase smoking cessation rates through incorporation of a smoking cessation program into a currently established mental health service for individuals with PTSD. Three, it increases the dose of the intervention without significant extra cost or time by using daily dosed written curricula. Finally, it tests the impact of a nurse-implemented MI counseling intervention.

This intervention attempts to alleviate barriers Veterans with PTSD face when accessing smoking cessation treatment. Its strength lies in its ability to provide smoking cessation and mental health care services via telehealth and the telephone. Providing care over the telephone is one way to increase availability of services. This intervention thereby facilitates the ease of interaction by providing in-home services, which decreases monetary and time resources spent traveling to a clinic for care. It also reduces potential stigma experienced when entering a VHA mental health clinic. Furthermore, it provides an opportunity for those living in very rural areas to utilize previously inaccessible smoking cessation treatment.

As smoking cessation interventions have been shown to be more successful when integrated into face-to-face mental health care visits [8], this intervention was designed to be *easily* implemented into current home telemonitoring mental health care. It is a comprehensive and intense approach that provides both mental health and smoking cessation services to Veterans with PTSD daily via the home telehealth platform, through weekly scheduled MI counseling calls, and, as needed, for immediate mental health issues and/or changes. It further tests the efficacy of the incorporation of smoking cessation care into mental health services by testing the delivery of an intervention over the phone and via telehealth. The Health Buddy platform is currently used nationally in the VHA for many diagnoses, including chronic obstructive pulmonary disease, congestive heart failure, diabetes and depression. It is a large chronic disease management initiative for the VHA; it was introduced in 2003 and aimed to have 92,000 enrollees by the end of 2012 [37]. Smoking cessation curricula could be easily added to any currently offered disease management program, and thus could reach many smokers quickly and easily. If shown to be effective, the ease of implementation of this program into currently in-use, established medical care is a strength of this intervention.

To our knowledge, limited studies have examined the effect of print-based MI interventions on behavior change. For this study, the research team wrote a smoking cessation curriculum using the tenants of MI. Smoking cessation assistance is administered via the telehealth appliance to the participant every day the Health Buddy is used for 90 sessions. Thus, the participant receives smoking cessation information more frequently than is typically administered in a class or counseling session. If successful, this method is a cost effective way to deliver frequent smoking cessation information to a large number of participants.

Nurses are ideal implementers because they have experience in teaching and increasing self-management and positive behaviors and have been shown to successfully manage chronic diseases via telehealth [38,39]. They have also been shown to improve health outcomes through the use of counseling and motivational approaches [18,40]. Additionally, because all care is telephone-based, the nurse is not bound by appointment times, allowing for more flexibility depending on individual needs of the patient. The average length of every phone call is recorded in the study. Ability of the care coordinators to deliver the intervention with high fidelity was tested and validated in the pilot study [18].

Another unique aspect of the study is its less restrictive inclusion criteria which increases its generalizability. All smokers, regardless of their desire to quit smoking are invited to participate, resulting in the potential to provide smoking cessation assistance to those who might not otherwise receive it. PTSD is often not a solitary diagnosis; 88% of men and 78% of women with PTSD also have at least one other mental health diagnosis [41]. Whereas some trials examining PTSD and smoking have excluded those with bipolar, substance abuse and schizophrenia, this study does not make a blanket statement to omit participants with those diagnoses. Ability to participate in a protocol, as decided by their current primary care or mental health provider, will allow participants with managed concurrent mental health diagnoses to participate. We loosened our inclusion criteria during the trial in order include participants who were smoking less than ten cigarettes a day. This change occurred to be more inclusive to interested participants. Thus, if successful, the results can be applied inclusively to a large population.

In conclusion, this study’s significance lies in its ability to test the incorporation of written and telephone MI based smoking cessation into an already established and utilized mental health care coordination program.

## Abbreviations

PTSD: Posttraumatic Stress Disorder
MI: Motivational interviewing
PACIC: Participant’s perception of care coordination
GDS: Geriatric depression scale
VR-12: Veterans Rand-12
